### 3.2. Overview of the Intervention

The psychological intervention will consist of seven group sessions, conducted weekly, with a duration of approximately 60 min each, with the exception of the first and last ones, which will last an hour and a half since they will involve carrying out the presentation and evaluation of the intervention, respectively. In turn, the program will be divided into three modules. Module 1: psychoeducation and awareness about perinatal mental health, which provides information on the prevalence of anxiety symptoms in the perinatal stage and the consequences for mothers and babies. Module 2: Management of emotions and thoughts. It covers three sessions and aims to provide strategies to identify and restructure those thoughts that harm us, as well as recognize the behaviors and emotions that they generate. Module 3: aimed at teaching how to solve problems effectively and communicate in the best possible way.

Throughout the sessions, relaxation training will be carried out in order to have a technique for reducing anxiety when it appears. Likewise, in all sessions, exercises will be assigned to do at home so that the participants can practice what they have learned each week. Finally, a closing session will be held in which the skills learned throughout the intervention will be reviewed. Each session will have a similar structure: review of homework assignments and resolution of problems that have arisen in this regard, explanation of the content of the session, practical exercises, homework assignment and relaxation training. The components of the intervention are described below and in Table 1.

Module 1: Psychoeducation and Awareness about Perinatal Mental Health

*Session 1: Learning about this new stage.* Welcome and a general presentation of the program and psychoeducation on the prevalence of emotional symptoms in the perinatal stage and its consequences for mothers and children. The role of hormones during motherhood will also be explained, both for the correct development of the pregnancy and its possible effects on physical and emotional levels. The activities will consist of debates and the normalization of emotions. The session will end with the practice of guided relaxation. As homework, an audio will be sent to practice relaxation.

Module 2: Management of Emotions and Thoughts

*Session 2: Becoming aware of my emotions*. Psychoeducation on the changes and demystification of the myths associated with motherhood. Information will be provided about the usefulness of emotions and their components. The changes and myths associated with motherhood will be discussed; the goal is to learn to identify and validate both positive and negative emotions. As homework, they will be given a self-reflection exercise to learn to identify the components of an emotion (physical, cognitive and behavioral parts), with the aim that they learn to detect emotions before they become uncontrollable. Additionally, an audio will be sent to practice guided relaxation.

*Session 3: Becoming aware of my thoughts I*. How they affect my emotions. Information will be provided about the formation of our thoughts and their relationship with our emotions. A metaphor about the functioning of negative thoughts will be read and discussed. The practical exercises will consist of interpreting a daily life situation and seeing how this interpretation affects your thoughts. As homework, they will self-record their thoughts and the emotions they have generated. Likewise, they will practice a new relaxation technique, diaphragmatic breathing.

*Session 4: Becoming aware of my thoughts II*. How they affect my behavior. Psychoeducation on thoughts will continue and cognitive distortions associated with this stage will be discussed. Some vignettes will be presented to identify how thoughts influence our emotions and behaviors. Techniques will be provided to generate alternative thoughts. Likewise, the functioning of behavioral activation will be explained. The practical part will consist of discussing the vignettes and generating alternative thoughts. On the other hand, they will be asked about pleasant activities to launch behavioral activation. As homework, they will generate alternative thoughts and record the emotions that accompany them. They will also perform diaphragmatic breathing and begin behavioral activation.

Module 3: Training in Problem-Solving and Assertiveness Skills

*Session 5: Deciding calmly.* Psychoeducation on how problems influence our mood and different coping strategies. Through practical exercises, it is intended that each woman identifies her way of making decisions and learning new strategies. The session will end by introducing a new relaxation technique, progressive muscle relaxation. As homework, alternatives will be generated for a daily problem raised during the session, behavioral activation will be maintained and, with the help of an audio recording, they will practice the new relaxation technique.

*Session 6: Learning to communicate better.* Information will be provided about the different forms of communication and their consequences. Through everyday situations, it is intended that each woman identify her way of communicating. Assertive communication strategies will be practiced. Homework will include practicing assertiveness in everyday life situations and practicing progressive muscle relaxation and behavioral activation.

*Session 7: More tools for this new stage.* The skills learned during the sessions will be reviewed. The expectant mothers will then be presented with a list of community support resources. Their interest and participation will be appreciated, and the group will end by carrying out the relaxation practice that they have chosen. Finally, the post-treatment evaluation will be carried out and the day for the first follow-up will be agreed upon.

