## Abstract

**Background:** Anxiety is one of the most frequent disorders during the perinatal stage that is associated with adverse health effects in women and their babies. In spite of this, preventive interventions during this stage are scarce. A long-distance intervention carried out during pregnancy can be an effective and accessible resource to help improve women’s emotional state. The objective of this study is to present and assess the effectiveness of a telepsychology cognitive–behavioral preventive intervention during pregnancy to manage anxiety. **Methods:** A random clinical trial will be carried out among pregnant women in Spain. The psychological intervention will take place via videoconference in seven weekly sessions, lasting one hour each, with groups of 6–8 pregnant women. Study outcomes will be collected via online questionnaires at five points in time: pre-intervention (baseline: t0), post-intervention (baseline: t1), follow-up at 1 month (t2), follow-up at 3 months (t3) and follow-up at 6 months (t4). The control group will receive usual pregnancy care (attendance at pregnancy follow-up consultations and information and answers to frequently asked questions provided by the midwife). Our primary hypothesis is that the intervention will decrease the frequency of women who present anxious symptomatology during pregnancy. The second objective is to analyze the effectiveness of this intervention to prevent depressive symptomatology during pregnancy, as well as postpartum anxiety and depressive symptomatology. The primary outcome measure is the difference in the mean anxiety score between the intervention and control groups assessed by the Edinburgh Depression Scale-Anxiety Subscale (EDS-3A), the State–Trait Anxiety Inventory (STAI) and Generalized Anxiety Disorder Screener (GAD-7) at the end of the intervention and at 1, 3 and 6 months postpartum. Generalized anxiety disorder (GAD) will be evaluated with the SCID clinical interview at the same time points. The secondary outcome will be determined by using the EPDS at the same time points. **Conclusions:** The results will determine whether a cognitive behavioral therapy applied via videoconference is well accepted by pregnant women, and if it is effective in preventing anxiety and emotional symptoms during the perinatal stage. If this intervention is an effective and useful resource among pregnant women, it can be implemented as a tool in Spanish healthcare.

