### 2.3. Outcomes and Allocation of Participants to Trial Groups

#### 2.3.1. Primary Outcome

The primary outcome measure will be the difference in the mean anxiety scores between the intervention and control groups assessed by the EDS-3A, STAI and GAD-7 questionnaire before and at the end of the intervention, and one month, 3 months and 6 months after the intervention. Generalized anxiety disorder (GAD) will also be evaluated through the DSM-5 clinical interview at the same time points. In this case, the percentages found will be compared.

The Edinburgh Depression Scale-Anxiety Subscale (EDS-3A) is the anxiety subscale of the Edinburgh Postnatal Depression Scale (EPDS) [42]. Different studies, e.g., [43,44] have found that three items (3, 4, 5) can detect anxiety in women during the perinatal period. Each of the three items has four response options (0 = none, 1 = somewhat, 2 = quite a bit, and 3 = a lot). The total score of the subscale ranges from 0 to 9. The cut-off point used in the EDS-3A to detect anxious symptomatology will be ≥5 [45].

The State–Trait Anxiety Inventory (STAI) [46] assesses both the current level of anxiety and the individual’s predisposition to suffering from anxiety. It consists of 40 items, 20 of which refer to the state subscale (STAI-E), with the other 20 referring to the trait subscale (STAI-R). The score for each subscale ranges from 0 to 60, with higher scores indicating higher levels of anxiety. In this case, the State Anxiety Subscale (STAI-E) will be applied; the recommended cut-off point for women is greater than 31 (75th percentile).

Generalized Anxiety Disorder Screener (GAD-7) [47] is a self-administered instrument consisting of seven items with four response options. The total score ranges from 0 to 21, with the highest scores being the most severe. The GAD-7 has been validated for use in Spanish-speaking pregnant women [48]. The cut-off point used to detect anxiety symptoms will be ≥7 [49].

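### The intervention arm's t1 evaluation follows a group relaxation practice in session 7, which can transiently lower state anxiety (STAI-E) in that arm only and favour it at t1

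*Protocol article*

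**What the plan says.** Section 3.2 of the protocol article gives the order of events in session 7. After the skills review and the list of support resources, "the group will end by carrying out the relaxation practice that they have chosen". The next sentence reads: "Finally, the post-treatment evaluation will be carried out and the day for the first follow-up will be agreed upon". The same section explains why the first and last sessions are longer than the others, "which will last an hour and a half since they will involve carrying out the presentation and evaluation of the intervention, respectively". It also gives the purpose of relaxation across the programme: "relaxation training will be carried out in order to have a technique for reducing anxiety when it appears".

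Section 2.3.1 makes three anxiety scales primary: EDS-3A, STAI and GAD-7. The STAI "assesses both the current level of anxiety and the individual’s predisposition to suffering from anxiety", and of its two parts only one is used: "In this case, the State Anxiety Subscale (STAI-E) will be applied". The group comparison is made "before and at the end of the intervention, and one month, 3 months and 6 months after the intervention", so t1 is one of the primary time points.

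The Abstract describes a different route for the data: "Study outcomes will be collected via online questionnaires at five points in time". Section 2.1 defines the control condition as usual care: follow-up appointments, midwife advice and group prenatal classes. The article describes no setting or date for the controls' t1.

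**The concern.** The two arms may be measured under different conditions at t1. In the intervention arm, a scale of momentary anxiety is listed straight after an exercise meant to reduce anxiety. In the control arm nothing comparable comes first. A short-lived drop in STAI-E would then be counted as programme effect. At t1 this drop coincides with arm, so comparing the arms cannot separate it from a lasting benefit.

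The t1 result matters for the primary objective, which is anxiety during pregnancy. The Abstract's primary-outcome sentence counts the later assessments from birth. On that reading t1 is the only measurement after baseline that falls in pregnancy. Section 2.8 also plans Cohen's d at each follow-up and a Reliable Change Index after treatment, and both would carry any distortion of the t1 STAI-E score.

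A second, smaller issue is reach. If t1 is completed in the last group session, a woman who has stopped attending may have a late t1 score or none.

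**Working it through.** **1. Is the session 7 evaluation t1?** Section 3.2 calls it post-treatment, and the date of the first follow-up is agreed at the same point. Follow-up starts at t2, so what precedes it is t1. The extra half hour (90 minutes instead of 60) is consistent with this. The explanation for that half hour speaks of evaluating the intervention, which could also cover the satisfaction questionnaire of section 2.3.2. The t1 reading is the natural one, but it is not free of ambiguity.

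**2. Which measures are exposed?**
- STAI-E: current anxiety, so directly exposed.
- GAD-7 and EDS-3A: the article gives no recall period, so exposure is not shown.
- SCID diagnosis of GAD: section 2.3.1 describes anxiety on most days over six months, so one exercise can hardly change it.
- t2 to t4: no session comes before them, so they are not exposed to this effect.

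**3. Sample sizes.** The plan's own figure comes first. For d = 0.55, two-sided α = 0.05 and 80% power with equal arms, the t-test calculation gives 52.87, so 53 per group; this reproduces section 2.7. Two groups of 53 make 106 women. At the 2:1 allocation of section 2.2, 106 women split into about 71 v 35, and the 140 to be recruited split into about 93 v 47.

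**4. What a transient drop would do.** The documents give no size for it. Assume that the lasting effect is zero and that the intervention mean is lowered by b SD at t1. For an unadjusted two-group test:

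SE = √(1/35 + 1/71) = √(0.02857 + 0.01408) = 0.2065

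P(significant) = P(|Z + b/SE| > 1.96)

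For b = 0.2: b/SE = 0.968, so P ≈ P(Z > 0.992) + P(Z < −2.928) ≈ 0.161 + 0.002 = 0.16.

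The exact t-test values are:

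| Assumed drop b (SD) | 71 v 35 | 93 v 47 | 53 v 53 |
|---|---|---|---|
| 0.1 | 0.08 | 0.09 | 0.08 |
| 0.2 | 0.16 | 0.20 | 0.18 |
| 0.3 | 0.30 | 0.38 | 0.33 |

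The nominal value is 0.05. The article gives no SD for STAI-E, so b cannot be converted into points on the 0 to 60 scale.

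**5. What missing non-attenders would do, if they were missing.** Bias in the arm mean = share missing × difference in mean between non-attenders and attenders. With an assumed 10% to 30% missing and an assumed difference of 0.2 to 0.5 SD, this runs from 0.10 × 0.2 = 0.02 SD to 0.30 × 0.5 = 0.15 SD. The documents give neither input, nor do they show the sign of the difference.

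**The case against.** The strongest reply is that the article does not fix immediate completion under the therapist's eye. Outcomes are said to be collected online at all five points, so the questionnaires could be answered after the call. The diagnostic interview is due at the same time points, and individual interviews of 6 to 8 women hardly fit into a 90-minute group session, so part of t1 must happen elsewhere. This stands as a reason for caution. It does not remove the problem, because the only written procedure for the intervention arm's t1 places it directly after relaxation.

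It can also be said that t1 is not the only test of the pregnancy objective. Sections 2.1, 2.3.1 and 2.8 count follow-up from the end of the intervention. Take the eligibility limit of 16 as weeks, add up to 6 weeks before the start and 7 weekly sessions, and t1 falls at up to about 16 + 6 + 7 = 29 weeks and t2 at about 33 weeks, normally still in pregnancy. On that schedule t2 tests the same objective without the session 7 effect. This stands, and it limits the consequence.

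Finally, section 2.8 plans repeated-measures analysis of variance with Bonferroni comparisons, not the single unadjusted test used above. The percentages therefore show direction and scale and are not the planned analysis's error rate.

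A reader might go further and infer that women who stopped attending are left out at t1. No section says so, and online collection could reach them. Nor does any section say that controls answer at home. The intervention women themselves join by videoconference, so a contrast of places has no support.

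**Conclusion.** The point holds in a limited form. As written, t1 in the intervention arm follows a relaxation practice that controls do not have, and this can bias the t1 STAI-E contrast towards the intervention. The direction rests on the protocol's own description of relaxation. The size is unknown: the range of 8% to 30% at 71 v 35 depends on an assumed drop of 0.1 to 0.3 SD, no lasting effect and an unadjusted test.

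The documents do not support a general claim that t1 is biased on all scales or that several biases all act in one direction. In a universal programme, the more distressed women might be the ones who stay, so the direction of any attender selection is open, as is that of therapist presence. One could also compute 24.3% × 93 ≈ 22.6 intervention women without a t1 score. That would use an attrition rate the article does not state (it is implied by 1 − 106/140) and would place all of it on session 7.

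The exposure is mainly one primary scale at one time point, plus a risk of missing or differently timed data. It should be fixed, but it does not put the trial as a whole in doubt.

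**What to change.** Reconcile the Abstract's online collection with the session 7 text in section 3.2. Take the t1 outcome questionnaires out of session 7. Send them online to every randomised woman in both arms in the same window, for example about one week after the group's planned last session, with controls on the matched date and regardless of attendance. Keep only the satisfaction questionnaire in session 7. The content of the session, including the relaxation practice, need not change.

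The cost is a change of wording and a scheduled message through the existing online route. The downside is small: some women may answer a few days later or need a reminder. The change has to be made before t1 data accrue, because an acute effect already in the t1 scores cannot be separated from the effect of the programme at that time point.

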## 4. Discussion

Perinatal anxiety is very common and can have important consequences for women, their children and their families [52]. To avoid these negative consequences, healthcare institutions and providers must emphasize the need to implement preventive interventions. Although pregnancy is a good time to carry out such interventions [56], during this period, help-seeking rates are low [16], mainly because most women are not aware of having a psychological problem and attribute their symptoms to pregnancy or childbirth. Barriers such as lack of information, the cost of conventional treatments or possible stigmatization also contribute to this [57,58].

Online interventions, including telepsychological interventions, offer advantages in overcoming the barriers mentioned above, facilitating access to reduced-cost interventions and offering greater flexibility [31]. Furthermore, these types of interventions make it possible to reach women who have more difficulty traveling to receive assistance [59] or have logistical problems attending in-person appointments [26,27], which allows adherence to be increased [39]. Likewise, group interventions have been shown to be effective in reducing emotional symptoms during this stage and show a high rate of compliance, acceptance and satisfaction on the part of women [8], in addition to reducing costs compared to an individual intervention [24].

However, telepsychological interventions also have limitations. Llerena and Ramos-Nobo [46] have classified them into five blocks: technical, ethical, sender, receiver and practical aspects. Considering the technical aspects, Maheu et al. [60] point out the need to have access to the internet and know how the devices used work, something that may not be available to everyone. Regarding ethical aspects, problems related to the privacy and/or confidentiality of information stand out [61,62]. Regarding the limitations associated with the sender, that is, the therapist, some resist integrating technological resources into professional practice [63] and/or do not have the competence (skills) to develop an intervention electronically [62]. Regarding the inconveniences related to the receiver, it should be noted that not all patients know how to use technological resources, nor are comfortable in the absence of face-to-face interactions [64]. Finally, on a practical level, the difficulty in establishing the alliance between patients and therapists and the difficulty in transmitting empathy stands out due to the absence of eye contact [65].

The therapies developed through videoconferencing make up for certain disadvantages of a purely online therapy, in which there is no direct contact with a professional, such as not offering direct interaction between the therapist and the patient, or attending to the needs that may arise during the same [32]. Therefore, whenever an online therapy is developed, it is important to consider the participation of a professional during the intervention and adapt it to the needs of women [66].

Likewise, knowing the high rate of comorbidity between anxiety and depression during the perinatal stage [6], a transdiagnostic intervention could be more beneficial than specific interventions for each disorder [37], as it allows addressing both symptoms simultaneously.

The therapies carried out over the internet do not replace face-to-face therapies developed in the clinical setting, although this modality can be a cost-effective, easily accessible and low-intensity resource for women who cannot receive standard psychological treatment.

This intervention is developed with the aim of contributing to increasing scientific evidence on the effectiveness of CBT applied by videoconference to prevent emotional symptoms during pregnancy and postpartum. This protocol aims to promote the prevention of anxiety and emotional symptoms associated with the perinatal stage. At the public health level, it is necessary to address maternal mental health and dedicate resources to provide tools to future mothers to cope with anxiety symptoms during the perinatal stage, which may reduce the possible adverse consequences that may arise from them.

## Figures and Tables

**Figure 1 jcm-13-05877-f001:**
[figure not shown]
Flow chart of the study design.

**Table 1 jcm-13-05877-t001:** Intervention components.

Module 1. Psychoeducation and Awareness about Maternal Mental Health			
Session 1. Learning about This New Stage			
Welcome	General Program Presentation		Psychoeducation
			-Information about emotional symptoms and their consequences during the perinatal stage -Hormonal changes -Relaxation
**Module 2. Management of Emotions and Thoughts**			
**Session 2**	**Session 3**		**Session 4**
**Becoming aware of my emotions**	**Becoming aware of my thoughts I**		**Becoming aware of my thoughts II**
-Information about the myths and changes associated with motherhood -Identify and validate your emotions -Relaxation	-Psychoeducation on the formation of our thoughts and their influence on our emotions -Identify your thoughts -Relaxation		-Psychoeducation on how thoughts affect our behavior and behavioral activation -Identify your cognitive distortions and learn strategies to generate alternative thoughts -Identify pleasant activities and begin behavioral activation -Relaxation
